### Endpoints

The primary composite endpoint of the study is the number of hospitalizations for re-ablation and cardioversion from baseline to 12 months after ablation. The conditions for performing a re-ablation and cardioversion are explained above.

Secondary endpoints are the number of hospitalizations for re-ablation, the number of cardioversions, the number of cancelled ablations because of overall symptom reduction, mortality, number of strokes, acute ischemic events, or hospitalizations for heart failure at 12 months after ablation.

Further secondary endpoints include change in weight, blood pressure and laboratory tests at baseline, after the lifestyle intervention (for the intervention group) and at 1 year after ablation. Furthermore, ablation success is determined at 12 months after ablation. The ablation is considered to be successful when patients can stop their antiarrhythmic drugs after 3 months, without having recurrence of symptomatic arrhythmias urging for re-ablation. The elaborate lifestyle changes might negatively affect treatment burden. Treatment burden is the perception of cumulative work a patient has to perform to manage their health, and should, therefore, be limited. Therefore, further secondary endpoints include the change in quality of life and treatment burden from baseline to before ablation, at 3 months, and 12 months after ablation. The patient’s general quality of life will be assessed with the Dutch version of the EuroQol-5D questionnaire. This questionnaire includes 5 health-state measures and is suitable to determine quality-adjusted life-years for a cost–utility analysis [31]. AF-specific quality of life is assessed with the Dutch version of the AF effect on Quality of Life Survey (AFEQT). This questionnaire is suitable for describing AF-related symptoms [32]. Treatment burden will be evaluated with a Dutch translation of the Treatment Burden Questionnaire.

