### Data collection

Assessment of clinical endpoints will take place at hospital visits during the intake, pre-ablation and the follow-up consultations at 3 and 12 months after ablation. Quality of life data will be collected using digital questionnaires at intake, pre-ablation, 3 months after ablation and 12 months after ablation.

An overview of the study procedures is displayed in Table 3.

**Table 3 Tab3:** Study procedures

Study procedure	Intake	Pre-ablation (only in interventional group)	3 months after ablation	12 months after ablation
Assessment of clinical history and clinical endpoints	x	x	x	x
Physical examination including blood pressure and weight	x	x		x
12-lead ECG	x		x	
Laboratory test	x	x		x
Quality of life using EuroQol-5D, AFEQT, Treatment Burden Questionnaire	x	x	x	x

*ECG* electrocardiogram

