### Statistical analyses

Descriptive statistics will be used to report baseline characteristics of the study population. The primary and secondary endpoints can occur during the entire participation period, which is from baseline to ablation (in the intervention group during the risk treatment; in the control group when patients await the ablation) and in 12 months after the ablation. The different pre-ablation durations amongst patients lead to different study participation periods. Therefore, the number of events will be normalized using the participation period and will be reported in numbers per year (the event rate). The clinical hypothesis that the intervention group will have a lower event rate will be tested by fitting a Poisson regression model to the event data and testing the effect of the intervention group using a Wald test. Results will be reported in terms of incidence risk ratios with accompanying 95% confidence intervals. The primary analysis will be on an intention-to-treat basis. Subgroup analyses will be performed on the primary endpoint. Covariates of interest in this study include gender, age, type of AF (paroxysmal vs. persistent) and number and extent of the respective modifiable risk factors as defined in Table 2.

The secondary endpoints will be analysed by means of chi-squared test or Fisher’s exact test depending on the number of occurrences. Changes in weight and blood pressure will be compared using the appropriate test (unpaired *t* test or Mann–Whitney *U* test), depending on the distribution of data. Laboratory tests will be analysed for differences by fitting linear mixed models to the data.

A cost-effectiveness analysis will be included, covering incremental cost-effectiveness ratio (ICER) and an evaluation of change in patient value, using the EuroQol-5D and AFEQT questionnaires and healthcare-related costs of intervention. Differences in medical hospital costs for both study groups will be compared using the appropriate statistical test (unpaired *t* test or Mann–Whitney *U* test), depending on the distribution of data. Cost savings associated with the study intervention will be calculated by subtracting the cost of the intensive treatment from the cost of the conventional treatment. The completed EuroQol-5D, AFEQT and TBQ questionnaires will be analysed for differences between treatment groups at different moments by fitting linear mixed models to the data.

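### Weight and blood pressure changes are compared without baseline adjustment; the test is valid, but ANCOVA on data already collected would be more precise, mainly for blood pressure

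*Protocol article*

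**What the plan says.** The Endpoints section makes change in weight and in blood pressure secondary endpoints: "Further secondary endpoints include change in weight, blood pressure and laboratory tests at baseline", with later measurements after the intervention period (intervention group only) and at one year after ablation.

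In Table 3 (Data collection), the row "Physical examination including blood pressure and weight" is marked at intake, pre-ablation and 12 months. The pre-ablation column is headed "Pre-ablation (only in interventional group"), so the comparison between arms runs from intake to 12 months.

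The Statistical analyses section then fixes the method: "Changes in weight and blood pressure will be compared using the appropriate test (unpaired *t* test or Mann–Whitney *U* test), depending on the distribution of" the data. No baseline covariate is named for these endpoints. The sentence that begins "Covariates of interest in this study include gender, age, type of AF (paroxysmal vs. persistent" directly follows the subgroup analyses of the primary endpoint and is not tied to weight or blood pressure. Laboratory tests, which have the same Table 3 schedule, go to linear mixed models instead.

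**The concern.** The article names the test, so this is a stated choice and not a detail left to an analysis plan that is not shown.

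A two-sample test on change scores subtracts the full baseline value, as if the regression of follow-up on baseline had slope 1. Where the slope is below 1, that over-corrects: the arm that starts higher by chance tends to show the larger fall, with no treatment effect. The variance is also larger than it needs to be.

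The switch to Mann–Whitney adds a second weakness. It changes the quantity being compared once the data have been seen, and it does not estimate a baseline-adjusted mean difference.

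Weight and blood pressure are direct targets of the intervention (Table 2). They help show whether the programme changed the risk factors it addresses, so a more precise estimate is worth having if it costs nothing.

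**Working it through.** **Inputs from the article.** Allocation is 1:1 and 150 patients are enrolled, so 75 per arm, taken here as all measured at 12 months. The significance level is 0.05, used here as two-sided. The article gives no SD, expected effect or power for weight or blood pressure, so there is no stated figure to reproduce.

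**Assumptions.** ρ is the correlation between baseline and 12-month values, with a range of 0.3 to 0.95. The variance σ² is equal at both times. Where mmHg are shown, the blood pressure SD is taken as 15.

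**Precision.** Per patient:

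- change score variance = 2(1−ρ)σ²
- ANCOVA variance = (1−ρ²)σ²
- ratio ANCOVA/change = (1−ρ²)/[2(1−ρ)] = (1+ρ)/2

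If a difference is one that the change-score test detects with 80% power, ANCOVA has power Φ(2.802/√[(1+ρ)/2] − 1.96). The number per arm with which ANCOVA matches 75 on change scores is 75(1+ρ)/2.

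| ρ | Variance ratio | Reduction | Matching n per arm (rounded) | ANCOVA power |
|---|---|---|---|---|
| 0.3 | 0.65 | 35% | 49 | 93.5% |
| 0.5 | 0.75 | 25% | 56 | 90% |
| 0.7 | 0.85 | 15% | 64 | 86% |
| 0.9 | 0.95 | 5% | 71 | 82% |
| 0.95 | 0.975 | 2.5% | 73 | 81% |

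A simulation with 75 per arm and 4,000 runs gave variance ratios of 0.73 at ρ = 0.5 and 0.96 at ρ = 0.9, close to the formula. In a second simulation on normal data at ρ = 0.5 (SD 15, true difference 6.9), power was 0.79 for the t test, 0.77 for Mann–Whitney and 0.89 for ANCOVA.

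**Without equal variances.** With SDs s₀ at baseline and s₁ at follow-up, change-score variance minus ANCOVA variance is (s₀² + s₁² − 2ρs₀s₁) − s₁²(1−ρ²) = (s₀ − ρs₁)². This is never negative, and it is zero only when the slope ρs₁/s₀ equals 1. So the direction of the precision result is general, but the table and the over-correction are not. Over-correction needs a slope below 1.

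**Baseline imbalance.** The standard error of the baseline difference is √(2/75) = 0.163 SD. A baseline difference D shifts the change-score estimate by −(1−ρ)D and leaves ANCOVA essentially unmoved. Simulated slopes on D were −0.52 and −0.10 for change scores at ρ = 0.5 and 0.9, against −0.02 and 0.00 for ANCOVA.

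Take D = 0.33 SD, which is 0.33/0.163 ≈ 2.02 standard errors and about 5 mmHg. A difference at least this large, in either direction, occurs in about 4% of randomisations. The rejection threshold is 1.96√[2(1−ρ)·2/75] and the SE conditional on D is √[(1−ρ²)·2/75]. In SD units:

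| ρ | Shift | Threshold | Conditional SE | Conditional type I error |
|---|---|---|---|---|
| 0.5 | 0.165 (2.5 mmHg) | 0.320 | 0.141 | 13.7% |
| 0.7 | 0.099 (1.5 mmHg) | 0.248 | 0.117 | 10.2% |
| 0.9 | 0.033 (0.5 mmHg) | 0.143 | 0.071 | 6.8% |

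With D = 0 and ρ = 0.5 the conditional error is P(|Z| > 1.96/√0.75) = 2.4%. Averaged over all imbalances it is 5%.

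**The case against.** The strongest objection is that nothing here is invalid. Under 1:1 randomisation the comparison of change scores is unbiased and keeps its 5% error, and the article makes no power claim for these endpoints that could be wrong. That stands: this is an improvement in efficiency, not the correction of an error. A reader might infer from the 14% figure that the planned test inflates type I error. It does not. The figure is conditional on an imbalance of about 2 standard errors and is offset by a conditional error below 5% when the arms are well balanced.

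The size is also assumed. Neither ρ, the SD nor the 80% starting power is in the article, and the gain in power points would be smaller from a starting power well above or below 80%. That stands too, and it is why a range is shown. For weight, which probably tracks closely, the gain is only 1 to 2 points of power.

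Three further inferences are tempting and not supported:

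- That Mann–Whitney ignores baseline. Applied to changes it uses baseline by subtraction; what it cannot do is estimate the slope. Its simulated cost on normal data was 2 points.
- That randomisation is unstratified and imbalance therefore more likely. A condensed article's silence does not show this.
- That the primary result could not be interpreted without this change. These are secondary endpoints, and a change-score result would still show whether weight and blood pressure moved.

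What the objection does not remove is that the article fixes a less precise test while the covariate is already collected.

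**Conclusion.** The point holds as a free improvement to two secondary endpoints. ANCOVA would reduce the variance by about 15 to 25% if ρ lies between 0.5 and 0.7, which is plausible for blood pressure, and by 2.5 to 5% if ρ lies between 0.9 and 0.95, which is more likely for weight. These percentages rest on equal variances at both times and on values of ρ that the article does not supply. ANCOVA also removes nearly all of the dependence on chance baseline imbalance. The primary Poisson analysis and the sample size are untouched. Priority is low to moderate.

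**What to change.** Replace the sentence on weight and blood pressure with wording such as:

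*Weight and blood pressure at 12 months after ablation will be compared between groups by linear regression (ANCOVA) with treatment group and the baseline value of the same measure as covariates. The adjusted mean difference will be reported with its 95% confidence interval. If residuals are clearly non-normal, a robust or bootstrap confidence interval for the same adjusted difference will be used.*

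This replaces the switch between t test and Mann–Whitney for these endpoints. The endpoints can still be described as changes: with baseline in the model, regressing the change or the 12-month value gives the same treatment coefficient.

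The cost is one sentence. No new data, visits or patients are needed, and linear regression is available in the named software.

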## Methods

### Trial design

The POP study is a prospective, open-label, single centre, investigator-initiated, randomized controlled clinical trial (NCT05148338). Eligible patients referred for catheter ablation by other cardiologists in non-interventional hospitals will be randomly assigned in a 1:1 ratio to usual current temporary care or an elaborate lifestyle intervention. If a patient experiences a major reduction in AF symptoms during the pre-procedural work-up, the cardiologist will counsel the patient whether the ablation should be cancelled. Patients from both study groups will undergo a PVI according to common clinical practise. After the ablation or from the moment of the decision of the cancellation of ablation, patients will be followed for 12 months. Follow-up visits will be performed at 3 and 12 months after ablation and consist of a physical examination next to laboratory tests and quality of life questionnaires. A detailed study flow chart is shown in Fig. 1. The trial is non-blinded, since blinding is not possible, given that the treating physician is involved in the multidisciplinary team.

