A *p* value < 0.05 will be considered statistically significant and all analyses will be performed using SPSS 29 (IBM SPSS Statistics 29.0, Chicago, IL, USA). We will use complete case analysis when the percentage of missing data is less than 5%. Otherwise, we will use multiple imputations by full conditional specification.

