### Sample size

The number of hospital admissions in the control group is estimated as 1.0 per patient per year [33, 34]. The proposed intervention is expected to reduce the primary endpoint with 30%. Taking the pre-ablation period into account, in the intervention group, we expect an overall event rate of 0.75 per patient per year. Assuming a balanced design with equal allocation of patients to the two groups, the minimum sample size to achieve an 80% power with 5% Type I error on the primary analysis is 144 (72 per treatment group). A total of 150 patients will be enrolled in this study, taking dropouts into account.

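### Hospital costs may be tested by Mann–Whitney, a rank test, although the ICER and the savings figure planned beside it are differences in mean cost

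*Protocol article*

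**What the plan says.** All of this stands in one paragraph of the Protocol article, Statistical analyses.

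- An economic evaluation is planned: "A cost-effectiveness analysis will be included, covering incremental cost-effectiveness ratio (ICER").
- Costs are to be tested between arms: "Differences in medical hospital costs for both study groups will be compared using the appropriate statistical test". The options given are "unpaired *t* test or Mann–Whitney *U* test), depending on the distribution of data".
- A savings figure follows: "Cost savings associated with the study intervention will be calculated by subtracting the cost of the intensive treatment from the cost of the conventional treatment".

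For all analyses, the significance rule is that a p "value < 0.05 will be considered statistically significant". The article gives no unit cost, no cost mean or SD, and no criterion for choosing between the two tests.

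**The concern.** The numerator of an ICER is a difference in mean cost. The savings figure is a subtraction of costs, so it too is a difference in means (or totals). The t test addresses that quantity. Mann–Whitney asks whether a patient drawn from one arm tends to rank above a patient drawn from the other, which is equivalent to comparing means only if one cost distribution is a shifted copy of the other.

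A pure shift is unlikely here. If programme costs are counted, nearly every intervention patient carries a modest extra cost (nurse visits, a cardiologist consultation, a home sleep test), while savings come from the patients who avoid an admission. The first effect moves many ranks a little. The second moves the mean a lot through few patients.

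At stake is a cost p value that does not belong to the cost difference printed beside it. It could be significant when mean costs are equal, or non-significant when a real saving exists.

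**Working it through.** The plan states no cost figure, so there is nothing to reproduce. The check is a constructed data set and a simulation.

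**Inputs from the article.** "A total of 150 patients will be enrolled in this study" and patients are "randomly assigned in a 1:1 ratio", so 150 / 2 = 75 per arm. Planned rates are 1.0 and 0.75 admissions per patient-year (Sample size). The level is 0.05, taken as two-sided because the article does not say.

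**Assumed inputs (no currency implied).** Base cost is gamma with mean 2,000 and SD 1,000. Each admission costs c, and the programme costs k in the intervention arm only. Planned rates are modelled as one-year Poisson counts. Where cancellations appear, the index ablation costs 10,000 and the stated share is cancelled in the intervention arm only. There were 2,000 to 4,000 trials per setting, and ranges span repeated runs.

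**True mean difference (intervention minus control).** k − c × (control events − intervention events) − 10,000 × share cancelled.

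**Constructed example.** Base 10,000, admission 12,000, programme 1,000, with one admission in 25 of 75 controls and 15 of 75 intervention patients.

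- Control mean: 10,000 + 12,000 × 25/75 = 14,000.
- Intervention mean: 11,000 + 12,000 × 15/75 = 13,400, a saving of 600 (Welch p = 0.49).
- Ranks: the 60 intervention patients at 11,000 exceed the 50 controls at 10,000 (3,000 pairs). The 15 at 23,000 exceed all 75 controls (1,125 pairs). So P(intervention > control) = 4,125 / 5,625 = 0.73, Mann–Whitney p = 1.8 × 10⁻⁷, in the direction of higher intervention cost.

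This shows that a reversal is possible. How often it happens depends on the setting:

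| Events, control vs intervention | c / k | Cancelled | True difference | Mann–Whitney p<0.05 | Welch p<0.05 | Mann–Whitney significant against observed mean |
|---|---|---|---|---|---|---|
| 1.0 vs 0.75 | 2,400 / 600 | 0 | 600 − 600 = 0 | 5–6% | 5% | 0% |
| 1.0 vs 0.75 | 5,000 / 1,250 | 0 | 1,250 − 1,250 = 0 | 14–16% | 5% | 0% |
| 1.0 vs 0.75 | 6,000 / 1,500 | 0 | 1,500 − 1,500 = 0 | 18–21% | 5% | 0.1% or less |
| 1.0 vs 0.75 | 10,000 / 600 | 0 | 600 − 2,500 = −1,900 | 5–6% | 21–22% | 0% |
| 1.0 vs 0.75 | 6,000 / 1,500 | 10% | 1,500 − 1,500 − 1,000 = −1,000 | 6% | 16% | 0.05% |
| 0.5 vs 0.35 | 6,000 / 1,000 | 5% | 1,000 − 900 − 500 = −400 | 26% | 8% | 5% |
| 0.5 vs 0.35 | 8,000 / 1,500 | 5% | 1,500 − 1,200 − 500 = −200 | 61% | 5% | 21% |
| 20% vs 14% of patients | 10,000 / 600 | 0 | 600 − 600 = 0 | 54–56% | 5% | 12–14% |
| 20% vs 10% of patients | 10,000 / 600 | 0 | 600 − 1,000 = −400 | 41–42% | 9–10% | 19–20% |

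Frequency matters because of the share of patients with no admission. At the planned rates this is exp(−1.0) = 37% of controls and exp(−0.75) = 47% of intervention patients, so admissions spread through most of the ranking. At 20% vs 10–14%, at least 80% have none, and the programme cost dominates the ranks.

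The equal-means results are not an upper bound. Inflation grows as the programme cost grows against the base spread. At planned rates with c = 10,000 and k = 0.25 × 10,000 = 2,500, Mann–Whitney rejected in 43% of 4,000 trials and significantly contradicted the observed mean in 2.6%.

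**The case against.** The strongest objection concerns magnitude. The trial plans for 1.0 vs 0.75 admissions, cardioversions included, so costly events are not confined to a small minority. At those rates significant reversals nearly vanish in the main settings. Cancelled ablations, a planned secondary endpoint and a further source of saving, do not bring them back. This stands. A reader might infer that the plan is likely to declare the intervention significantly costlier while it saves money. The documents do not support that: it needs event rates well below the plan's own, or large assumed programme costs.

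A reader might also infer that the p value is meant to support the ICER or the savings figure. The article does not say so. It lists three items in one paragraph, and the link is only their position. The tested quantity is hospital costs, whereas the ICER draws on health-care costs of the intervention. If the tested cost leaves out the programme, the shift that drives the rank disagreement disappears. The article does not settle this.

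The choice of Mann–Whitney is likely but not certain, since no criterion is given and the t test remains open. Finally, the absence of a stated uncertainty method for the ICER is no fault in a condensed article, because a health-economic plan may hold it.

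What survives is that the article names a rank test as an option for costs. That is a stated rule and not an omitted detail, and a rank test does not test a difference in mean cost at any event rate.

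**Conclusion.** The point holds as a mismatch between test and reported quantity, of minor severity. Skewed costs would probably send the analysis to Mann–Whitney, whose p value does not refer to the mean cost difference.

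At the planned 1.0 vs 0.75 admissions, with equal true means and admission costs of 2,400 to 6,000, rejection is about 5–22% against about 5% for Welch. With a true saving, the harm is lost power, about 6% against 22% in the 10,000 / 600 setting. Significant contradictions of the observed mean are 0.1% or less in these settings. Rejection of about 40–55% and contradictions of about 12–20% arise if costly events occur in only 20% vs 10–14% of patients and programme costs are in the tested cost.

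All of these sizes rest on assumed costs. The primary endpoint and the sample size are not affected.

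**What to change.** In Statistical analyses, delete the Mann–Whitney option for costs. Compare arithmetic mean costs whatever the skew, and report the mean difference with a 95% CI. A bootstrap interval, a Welch interval or a mean contrast from a generalised linear model would each do. State that the tested cost uses the same definition as the savings figure, including whether programme costs are counted.

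This changes analysis wording only, with no new data or patients. The downside is a wide interval, which reflects how imprecisely a trial of 150 patients measures mean cost.

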### Sample size

The number of hospital admissions in the control group is estimated as 1.0 per patient per year [33, 34]. The proposed intervention is expected to reduce the primary endpoint with 30%. Taking the pre-ablation period into account, in the intervention group, we expect an overall event rate of 0.75 per patient per year. Assuming a balanced design with equal allocation of patients to the two groups, the minimum sample size to achieve an 80% power with 5% Type I error on the primary analysis is 144 (72 per treatment group). A total of 150 patients will be enrolled in this study, taking dropouts into account.

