## Background and rationale

The management of atrial fibrillation (AF) is complex and many patients experience recurrence of symptoms after an invasive treatment with catheter ablation [1]. Although general outcomes of AF ablation have improved over the years, due to innovations of ablation techniques, recurrence of arrhythmias is still experienced by at least one in five patients [2, 3]. The prevalence of AF in Europe is currently estimated at 8 million and is expected to rise to 10 million in a decade [4]. Therefore, more effective therapeutic strategies are required.

Several lifestyle risk factors have previously been identified as promoters of AF. These risk factors include obesity, physical inactivity, sleep apnoea, hypertension, smoking, alcohol use and diabetes mellitus [5–9]. In patients with body mass index (BMI) above 27 kg/m^2^, weight loss and general lifestyle advice leads to cardiac reverse remodelling and a reduction in AF symptom burden [10]. Furthermore, sustained weight loss reverses the natural progression of AF and improves arrhythmia-free survival [11, 12]. Likewise, physical inactivity independently increases the risk of AF [13]. Individuals with better cardiorespiratory fitness have a decreased risk of AF recurrence and experience less severe symptoms [14, 15]. In addition, obstructive sleep apnoea (OSA) has a severe, negative impact on AF treatment. Patients receiving OSA treatment are less likely to progress to more permanent forms of AF [16]. OSA treatment with continuous positive airway pressure (CPAP) significantly decreases AF recurrence rates after pulmonary vein isolation (PVI) [17, 18]. Comparably, beneficial AF outcomes are observed if hypertension is strictly managed, if tobacco use is quitted or if alcohol consumption is decreased [19–21].

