### Post-ablation care

Patients of either treatment group will visit the outpatient clinic at 3 months after ablation. At this point, the treating physician will stop any current antiarrhythmic medication. If the patient does not experience any symptoms after ablation, no additional rhythm assessment will be performed, since this will not have therapeutical consequences. In symptomatic patients, arrhythmias will be objectivated with electrocardiogram or multiple holter assessments. If an arrhythmia is confirmed on electrocardiogram or holter after 3 months after the index ablation, patients are offered to recontinue antiarrhythmic medication and to undergo a repeat ablation. Furthermore, patients suffering from persistent AF will undergo cardioversion.

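### The sample size rests on a control rate labelled as hospital admissions; the article does not show that 1.0 per patient-year is the rate of the re-ablation and cardioversion endpoint, and the stated 80% power is sensitive to it

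*Protocol article*

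**What the plan says.** The Endpoints section defines the outcome: "The primary composite endpoint of the study is the number of hospitalizations for re-ablation and cardioversion from baseline to 12 months after ablation". Strokes, acute ischemic events and heart-failure hospitalizations are listed there as secondary endpoints. The Conclusion repeats the restriction to re-ablation and cardioversion.

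The Sample size section begins from a differently labelled quantity: "The number of hospital admissions in the control group is estimated as 1.0 per patient per year", with two literature citations. It continues "The proposed intervention is expected to reduce the primary endpoint with 30" percent and, allowing for the pre-ablation period, "we expect an overall event rate of 0.75 per patient per year" in the intervention group. From these it concludes that "the minimum sample size to achieve an 80% power with 5% Type I error on the primary analysis is 144 (72 per treatment group"), and 150 patients are to be enrolled to allow for dropout.

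Statistical analyses specifies a Poisson regression with a Wald test, with events counted from baseline, through the wait for ablation, to 12 months after it.

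The only other figure that bears on the event rate is in Background and rationale: "recurrence of arrhythmias is still experienced by at least one in five patients".

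**The concern.** A Poisson comparison draws its information from the number of events. The control rate therefore fixes the variance of the log rate ratio and the absolute difference. It does not fix the relative effect, which the section states separately.

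The label on the 1.0 covers a wider class of event than the endpoint. If the composite occurs less often than 1.0 per patient-year, the trial collects proportionally fewer events than planned. A null result could then say little even if the intervention achieves the assumed relative reduction.

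The article's own recurrence figure raises the doubt. The Post-ablation care section makes the offer of a second ablation, like that of renewed drug treatment, depend on a documented recurrence: "If an arrhythmia is confirmed on electrocardiogram or holter after 3 months after the index ablation, patients are offered to recontinue antiarrhythmic medication". Patients without symptoms get no extra rhythm assessment. One endpoint event per patient per year is a lot to expect where recurrence is of the order of one in five.

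**Working it through.** **Inputs from the article.** Control rate λ0 = 1.0 and intervention rate 0.75 per patient-year (rate ratio 0.75); n = 72 per arm; 5% type I error; equal allocation ("Assuming a balanced design with equal allocation of patients to the two groups"). Follow-up is 12 months after ablation. In the intervention group the ablation takes place at most 6 months after enrolment.

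**Assumptions.** Two-sided test (sidedness is not stated). Mean exposure T is 1.2 to 1.5 years, the same in both arms. There is no overdispersion. Control rates below 1.0 are illustrative; the article gives none.

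**Step 1: the plan's own figure.** For the Wald test of the log rate ratio,

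n per arm = (1.96 + 0.8416)² × [1/(λ0·T) + 1/(λ1·T)] / (ln RR)².

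With 1.0 versus 0.75:
- T = 1.0: 7.849 × (1 + 1.333) / 0.0828 ≈ 222 per arm.
- T = 1.5: ≈ 148 per arm.

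The stated 72 per arm is not reproduced. It would need about 221.3/72 = 3.1 years of exposure per patient. With the 30% reduction taken directly (RR 0.70), the formula gives about 150 (T = 1.0) and 100 (T = 1.5) per arm. The 80% is therefore not delivered even if 1.0 is accepted.

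**Step 2: sensitivity to the control rate.** With SE = √[1/(72·λ0·T) + 1/(72·0.75·λ0·T)], power = Φ(|ln 0.75|/SE − 1.96). The 95% confidence limits are the estimate divided and multiplied by exp(1.96·SE).

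Example, λ0 = 1.0, T = 1.2: expected events are 86.4 and 64.8; SE = √(1/86.4 + 1/64.8) = 0.164; 0.2877/0.164 = 1.751; power = Φ(−0.209) = 41.7%.

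| Control rate | Control events, T = 1.2 / 1.5 | Power, T = 1.2 / 1.5 | CI factor, T = 1.2 / 1.5 |
|---|---|---|---|
| 1.0 | 86 / 108 | 41.7% / 49.9% | 1.38 / 1.33 |
| 0.6 (assumed) | 52 / 65 | 27.3% / 32.9% | 1.52 / 1.45 |
| 0.4 (assumed) | 35 / 43 | 19.7% / 23.5% | 1.66 / 1.58 |

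With the more favourable RR of 0.70, power at a rate of 0.4 is still about 27% to 32%.

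**Step 3: how the recurrence figure compares with 1.0.** If 20% recur and each has one re-ablation and one cardioversion, the post-ablation year yields 0.20 × 2 = 0.4 events per patient. To reach 1.0 in that year would take 1.0/0.20 = 5 procedures per recurring patient, or 50% recurrence with two each.

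Events during the wait also count. With 0.4 events after ablation and an assumed wait of 0.2 to 0.5 years, an overall rate of 1.0 needs 1.2 − 0.4 = 0.8 to 1.5 − 0.4 = 1.1 events per patient before ablation. That is not impossible, but the article offers no figure for it.

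**The case against.** The strongest reply is that the 1.0 already is the composite rate. The endpoint is itself a count of hospitalizations, so admissions is natural shorthand. The next sentences apply the reduction to the primary endpoint and arrive at an overall event rate. The section never says all-cause, and the cited sources, which would settle the matter, are not at hand. This stands. A reader might infer that the plan used an all-admission rate in error, and might then charge the whole drop in power from 1.0 to a lower rate to that error. The documents do not support either step: if 1.0 is the composite rate, that loss is zero.

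The recurrence comparison is also weak as a refutation. It is a lower bound on the proportion of patients with recurrence after ablation in general. The 0.4 built on it leaves out pre-ablation events, repeat events in one patient, and cardioversions in the first 3 months. The sentence on cardioversion for persistent AF does not repeat the after-3-months condition set for repeat ablation. The trial also selects symptomatic patients with a high AF burden. So 0.4 is a scenario, not an estimate.

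What remains is that the label and the endpoint differ, no rate is explicitly tied to the composite, and the power claim depends heavily on that rate. Either reading calls for a correction: to the wording if 1.0 is the composite rate, to the input if it is not.

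**Conclusion.** The point holds as a statement about an unconfirmed input and a sensitive power claim, not as proof of a wrong input. Whether 1.0 applies to the composite cannot be settled from the article; it may be optimistic.

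At 1.0 the planned size gives about 42% to 50% power rather than 80%. That shortfall comes from the sample-size arithmetic and not from the choice of rate. Correcting the arithmetic alone would still carry an unconfirmed rate forward: power would be about 27% to 33% at 0.6 and 20% to 24% at 0.4. These figures rest on a two-sided test, a rate ratio of 0.75, equal exposure of 1.2 to 1.5 years and pure Poisson variation. Only the row for 1.0 uses the plan's own control rate.

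**What to change.** In the Sample size section:

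- State the expected control rate of hospitalizations for re-ablation plus cardioversion, covering the periods before and after ablation, with its source (for example the centre's own records). Alternatively, confirm that 1.0 is that rate.
- Replace the 80% claim with the power for the fixed 150 patients over a range of control rates, for example 0.4, 0.6 and 1.0 per patient-year. Give the assumed exposure and the sidedness of the test.
- Add the expected confidence-interval width or the detectable rate ratio at each rate.

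This costs a few lines of recalculation and a revised paragraph. Enrolment need not increase and no trial procedure changes. The downside is a less favourable stated power.
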